**Figure 2 F2:**
[figure not shown]
Illustration showing how patients may contribute to the different groups for incidence and prevalence. The blue arrows show total unexposed time in the study; the red arrows indicate exposure to warfarin; the purple arrow indicates exposure to DOAC. The vertical arrows show the yearly incidence and prevalence calculations, and the letters in boxes correspond to the group the patient would contribute to for that year. Incidence and prevalence for the first D then prevalence only for all subsequent Ds. D, denominator; DOAC, direct oral anticoagulant; I, incidence numerator, P, prevalence numerator; X, left the study.

#### ​Objective 2: to describe switching between OACs during the study period

The number and percentage of patients switching from warfarin to DOAC, DOAC to DOAC and DOAC to warfarin will be calculated. The number of patients with multiple switches and details of the switches will be described. The average time to switch will be reported.

#### 
*​*Objective 3: to compare the characteristics of patients with AF who were newly started on OACs during each period described in objective 1, to those who were not prescribed anticoagulation in the same period

Demographics, characteristics, comorbidities and concomitant medications will be reported for the three time periods described. Prevalent OAC users will be excluded from this part of the study as we want to compare those started on an OAC with those who are not during each time period.

Patients may contribute data to more than one group, but they will be censored at the time they are prescribed their index OAC. For example, they may enter the study during the first time period but may not be prescribed an OAC until period 3. In this case, they would contribute data to the no-OAC group in time periods 1 and 2 and then one of the OAC groups in period 3. If they entered in period 1 and started on an OAC in period 2, they would contribute data to the no OAC group in period 1 and the OAC group in period 2; they would not contribute any data to period 3 as they would be censored. Figure 3 illustrates how patients contribute to different groups during their time in the study. Patient demographics (age and biological sex) and characteristics (BMI, smoking status and alcohol consumption) will be reported as percentages in predefined categories. The proportion of the cohort with each of the comorbidities and concomitant medications will be described. The mean CHA_2_DS_2_-VASc and HAS-BLED scores will be reported.

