## Abstract

**Introduction:**

Warfarin has frequently been underused in older people for stroke prevention in atrial fibrillation (AF). Direct oral anticoagulants (DOACs) entered the UK market from 2008 and have been recommended as an alternative to warfarin. This study aimed to describe any changes in the prescribing of oral anticoagulants (OACs) to people aged ≥75 years in UK general practice before and after the introduction of DOACs, to examine differences in patient characteristics which may influence prescribers’ decisions regarding anticoagulation, to evaluate the time people stay on OACs and switching between OACs.

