### Source population

The study period will start on 1 January 2003 and will end on 27 December 2017. The source population will consist of all patients in CPRD who have ≥1 Read codes for AF and have contributed a minimum of 12 months’ research standard data prior to entry into the cohort. To be eligible to join the study, patients need to have the following: a Read code for AF recorded during or any time prior to the start of the study period; evidence to support the diagnosis of AF, such as a second AF diagnosis at a later date, an echocardiogram or prescription for a rate limiting or antiarrhythmic medication in the 3 months before the AF diagnosis or anytime after; and age of ≥75 years at study entry.

Patients will enter the cohort at the latest of the following dates:

Start of the study period.First AF diagnosis.75th birthday.A year from the date they started to contribute research standard data.

Patients will be censored if they leave the practice, the practice stops contributing data, at their date of death or at the end of the study. For the incidence calculations and comparison of patient characteristics, patients will be censored when they are prescribed an OAC.

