#### ​Incident and prevalent users

Exposure status will be defined at cohort entry as

‘No OAC’, where the patient had at least a year free of OAC prior to study entry and does not receive an OAC during the study period.‘Incident OAC users’, where the patient had at least a year free of OAC prior to study entry then was prescribed an OAC during the study period.‘Prevalent OAC users’ if the patient received an OAC in the year prior to study entry.

Exposure status for incident OAC users will be stratified at the start of each study period to no OAC, warfarin or DOAC.

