### Covariate classification

It is recognised that some patients may remain in the cohort for a long time and their covariates may change. Therefore, covariates will be identified separately for each of the time periods the patient contributes data and will be grouped by DOAC, warfarin or no OAC, depending on exposure for that period.

We want to investigate whether certain comorbidities influence the prescribing of OACs. We will therefore look for comorbidities accumulated up to the end of the time period for patients who do not receive an OAC or the OAC index date where one is prescribed. Patients will be classified as having a comorbidity if the patient record contains ≥1 diagnostic Read code for a disease or ≥3 Read codes supporting the presence of the disease at any time prior to the relevant date for that period. Read codes used to support the presence of disease include attendance at specialist clinics (eg, diabetes clinics) or codes related to follow-up, such as hypertension monitoring.

Concomitant medication will be classified as≥1 prescription issues for a medication of interest in the 3 months prior to study entry, commencing an OAC, or the end of the time period. We will describe medications at study entry as baseline and then in each time period for the no OAC and incident OAC patients as described for the comorbidities previously mentioned. The medications of interest affect either stroke or bleeding risk or commonly interact with OACs (antihypertensives, antiplatelets, statins, diabetic medications, antiarrhythmics, non-steroidal anti-inflammatory drugs, corticosteroids, anticonvulsants, systemic azoles, HIV protease inhibitors and ciclosporin).

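### Objective 3 counts patients who die or leave soon after entry as full members of the no-OAC group, so its table cannot show which traits influence prescribing

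*Protocol article*

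**What the plan says.** All locations are in the protocol article.

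- **Exposure, Incident and prevalent users.** No-OAC status is defined by absence of a prescription alone: "where the patient had at least a year free of OAC prior to study entry and does not receive an OAC during the study period". No minimum time under observation after entry is required.
- **Source population.** Entry is staggered (study start, first AF diagnosis, 75th birthday, or one year of research-standard data, whichever is latest). Exit can come at any time: "Patients will be censored if they leave the practice, the practice stops contributing data, at their date of death", or at study end. In addition, "For the incidence calculations and comparison of patient characteristics, patients will be censored when they are prescribed an OAC".
- **Statistical analysis, Objective 3.** Allocation is by period. For a patient who enters in period 1 and starts in period 3, "they would contribute data to the no-OAC group in time periods 1 and 2 and then one of the OAC groups in period 3". The outputs are descriptive: "The proportion of the cohort with each of the comorbidities and concomitant medications will be described", demographics are given as percentages, and for CHA2DS2-VASc and HAS-BLED the mean "scores will be reported".
- **Purpose.** The abstract sets out "to examine differences in patient characteristics which may influence prescribers’ decisions regarding anticoagulation". Covariate classification says: "We want to investigate whether certain comorbidities influence the prescribing of OACs".
- **Statistical analysis, Objective 1.** Incidence uses person-time at risk, cut off at the first OAC prescription, but is stratified by age and sex only.

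**The concern.** Being in the OAC group requires staying alive and registered long enough to be prescribed one. Being in the no-OAC group requires nothing beyond entry. The plan says patients are censored, but censoring has no effect on a simple proportion: a short record and a five-year record each count once.

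If dementia, renal disease, heart failure or previous bleeding shortens follow-up, it will be more common among the untreated even where prescribers give it no weight. The reader would then take higher mortality for reluctance to anticoagulate, which is the question the study sets out to answer. The problem concerns who is in each group, not when covariates are read; it would remain if every covariate were fixed at entry.

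The end of each five-year period is a second source of short observation. A patient diagnosed in mid-December 2007 and started in January 2008 is no-OAC for 2003–2007. This mixes patients about to be treated into the comparator, but it favours one direction only for traits linked to entry date.

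**Working it through.** The protocol states no initiation, death or transfer rates and no numerical result for Objective 3, so there is no figure to reproduce. All rates below are assumptions. The trait is given **no effect on prescribing** throughout and has 20% prevalence. Odds ratios compare the trait in no OAC v OAC, so the true value is 1.0.

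**1. Closed form, constant rates.** Let L be the OAC initiation rate per year, m the death-or-leaving rate, and h = L + m.

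- Observed from the start of a 5-year period: P(OAC) = (L/h) × (1 − e^(−5h))
- Entry uniform over the period: P(OAC) = (L/h) × [1 − (1 − e^(−5h))/(5h)]

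Take L = 0.20, with m = 0.10 without the trait and 0.30 with it (exit tripled).

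- Full period, no trait: 0.6667 × (1 − 0.2231) = 0.518. Trait: 0.4 × (1 − 0.0821) = 0.367. Odds ratio = (0.518/0.482)/(0.367/0.633) = 1.85. Trait prevalence is 24.7% in no OAC v 15.1% in OAC.
- Uniform entry, no trait: 0.6667 × (1 − 0.7769/1.5) = 0.321. Trait: 0.4 × (1 − 0.9179/2.5) = 0.253. Odds ratio 1.40; prevalence 21.6% v 16.5%.

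In this scenario 23% (full period) to 40% (uniform entry) of the no-OAC group have under one year of follow-up in the period.

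**2. Trait that doubles exit (m = 0.08 v 0.16), L from 0.05 to 0.40.** Uniform entry gives odds ratios of 1.14 to 1.19; full period gives 1.23 to 1.54.

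**3. Simulation with other initiation patterns.** One million patients per scenario; none or half present from the period start and the rest entering uniformly; exit 10–20% per year, doubled by the trait.

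| Initiation pattern | Odds ratio, no OAC v OAC |
|---|---|
| Half would ever start, mean 3–12 months | 1.04 to 1.25 |
| All start at a constant 10–20% per year | 1.17 to about 1.5 |

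With exit tripled, the two ranges become 1.08–1.48 and 1.37–1.99. In the first pattern with exit doubled, about 14–28% of the no-OAC group have under 6 months between entry and exit or period end, and up to about 13% start only after the period ends.

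**4. Period end alone.** With equal exit (0.10), compare uniform entrants with those present from the start. For L = 0.10, P(OAC) is 0.184 v 0.316; the odds ratio for being untreated is (0.316/0.684)/(0.184/0.816) = 2.05. For L = 0.20 (0.321 v 0.518) it is 2.27. A trait tied to late entry is therefore distorted; one unrelated to entry date and exit is not.

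**5. Does using time at risk remove it?**

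- Constant initiation, scenario in step 1: rates were 0.201 per year with the trait and 0.200 without, against a true 0.20.
- A Cox model for time to first OAC in four scenarios gave hazard ratios of 0.99 to 1.01, where the table odds ratios were 1.08, 1.10, 1.30 and 1.29.
- Restricting to patients who entered at least 6 months before period end did not help: 1.09, 1.11, 1.32 and 1.31.
- If starts cluster soon after entry (first pattern in step 3, exit doubled), crude rates overshoot: rate ratios of 1.06 to 1.30 in further runs at 10% and 20% exit. Splitting person-time by time since entry brought them to 1.00–1.01.

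**The case against.** The strongest reply is that the analysis does what Objective 3 literally says. It compares starters with patients not prescribed an OAC in the same period, by percentages and means, with no odds ratio or model. On that reading, the December 2007 patient is classified correctly. This stands: the table is a valid description.

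A reader might infer that the protocol treats every no-OAC patient as an observed decision not to treat. It never says so; the difficulty arises only when the table is read for the stated aim. A reader might also infer that reaching the period end makes frailty look like a deterrent in the way that early death does. It does so only for traits linked to entry date. Nor has any distortion of the comparison between periods been calculated.

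The quoted example follows a patient through three periods. It shows that allocation ignores observation time, but not how early leavers are handled; that follows from the entry, exit and no-OAC definitions. Figure 3, which marks patients leaving, is not shown.

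The effect can be small. At the lower end for a doubled exit rate, prevalence is about 20.3% v 19.7%. If most starts follow closely on entry, little bias remains.

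The purely descriptive defence does not fully hold, because the abstract and Covariate classification both state an aim about influence on prescribing. Downstream harm is limited: Objective 4 takes covariates from Objective 3, but that comparison is among starters only.

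**Conclusion.** The point holds as a limit on interpretation. Under the written rules, any trait that shortens follow-up is over-represented in the no-OAC group even with no effect on prescribing, so the table cannot by itself support statements about what influences prescribing. For traits that shorten follow-up the direction was the same in every scenario examined. The size cannot be taken from the documents: about 1.04 to 1.5 on the odds ratio scale for a trait that doubles exit, and more for stronger effects on exit, given the assumed rates and a 20% trait. This is not a detail left to an analysis plan, because the article itself fixes both the grouping and the summary measures. The Objective 1 person-time incidence by age and sex does not share the problem of counting each patient once regardless of follow-up, but it does not cover comorbidities, risk scores or medication.

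**What to change.** In Statistical analysis, Objective 3:

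1. Keep the descriptive table.
2. Add, for each period, OAC initiation rates per person-time at risk by characteristic, split by time since entry, or rate or hazard ratios from a time-to-first-OAC model with delayed entry at the period start. Censor at death, leaving and period end. Give 95% CIs.
3. Take characteristics as known at the start of at-risk time in the period, or update them during it.
4. Base statements about influence on prescribing on these results.
5. Report median at-risk time per group, and state that the no-OAC group includes patients with little observation time.

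Excluding late entrants is not a substitute, since early death or leaving drives the bias.

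**Cost.** No new data source; the at-risk time is already needed for Objective 1. Characteristics are currently read at the index date or period end, so they must also be derived at the start of at-risk time, which is the main extra work. Separate warfarin and DOAC models would add more and are optional. Rates are slightly less simple to read than percentages.

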## Introduction

A large body of evidence has shown that vitamin K antagonists (VKAs) are safe and effective for stroke prevention in atrial fibrillation (AF), but they have frequently been underused in older people.^1^ Reasons cited by physicians as making them less likely to prescribe VKAs for a person with AF include advancing age, risk of falls, comorbidities and previous bleeding.^2^

The first direct oral anticoagulant (DOAC), dabigatran, was marketed throughout Europe and in the UK in 2008, but was not licensed for stroke prevention in AF until 2011. Since then, three additional DOACs have been licensed for prevention of stroke: rivaroxaban, apixaban and edoxaban, and these are recommended in national and international guidelines as an alternative to warfarin.^3–5^ In the UK, the National Institute of Clinical Excellence (NICE) produces technology appraisals making recommendations for new medicines. The National Health Service is legally obliged to fund those medicines recommended by NICE within 3 months of publication of the appraisal. NICE published favourable technology appraisals for dabigatran and rivaroxaban in 2012,^6 7^ apixaban in 2013^8^ and edoxaban in 2015,^9^ meaning DOACs were available across the UK from mid-2012 onwards for stroke prevention in AF.

DOACs may allay some prescribers’ concerns when deciding whether to anticoagulate their older patients: they have fixed dosing schedules and can be added to compliance aids. They have also been shown in clinical trials to have a significantly lower risk of intracranial haemorrhage than warfarin^10–13^ (a prominent concern in patients with a history of falls).^14^

Since the introduction of DOACs, the overall rate of oral anticoagulant (OAC) initiation has increased by 58%.^15^ However, it is not known whether the introduction of DOACs has changed the rates of OAC prescribing for older people (aged ≥75 years) or how patient demographics, comorbidities and concomitant prescribing affect the choice of anticoagulant prescribed in UK general practice.

This study aimed to characterise prescribing of OACs to people aged ≥75 years in UK general practice, before and after the introduction of DOACs.

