### Statistical analysis

#### Objective 1: to describe changes in the point prevalence and incidence of OAC prescribing by year prior to the introduction of DOACs (2003–2007), between the introduction of DOACs and the time they were recommended by NICE for stroke prevention in AF (2008–2012), and following NICE recommendation (2013–2017).

Only patients prescribed an OAC will contribute data to the incidence and prevalence calculations. For incidence, patients may only contribute to either the warfarin or the DOAC group once as they will be censored at the time they are prescribed an OAC. The point prevalence will be calculated at the midpoint of each year so will take account of switching. For prevalence, a patient could contribute to the warfarin group for some years, and the DOAC group for other years. Prescription mapping will be used to calculate the number of people with an OAC prescription that includes that time point as the numerator and the total number of people in the cohort at that time point as the denominator.

The incidence of OAC prescribing will be calculated overall and for each specific OAC. Everyone in the cohort will be considered ‘at risk’ until the time they receive their first OAC prescription. Incidence will be calculated using the number of incident OAC users as the numerator and person-time at risk for non-exposed persons as the denominator. For the person-time at risk calculation, the denominator will be truncated at the date of their first OAC prescription. Incidence will be stratified by age (75–84 and 85+) and sex.

Figure 2 illustrates how patients may contribute to the incidence and prevalence calculations throughout the study.

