## Discussion

A number of studies have described changes in anticoagulation prescribing in the time since DOACs were introduced in the UK.^15 27 28^ However, none have focused specifically on their use in older people aged ≥75 years, despite older people being the largest users of anticoagulants for AF. The main strength of this study is that it will investigate prescribing in a large cohort of older patients using the CPRD, which is generally representative of the UK population. This study will look at a number of different factors that may influence the prescribing of anticoagulants and how these have changed over time. The results of this study will inform future comparative studies between OACs as it will provide an insight to potential confounders which may need to be controlled for. A limitation of this study is defining accurately when patients are exposed to an anticoagulant and when they are not. This is particularly difficult for warfarin as dosing information is not included in the CPRD. A number of studies have compared DOACs and warfarin using routinely collected healthcare data, but they do not describe how they mapped warfarin exposure.^29 30^ This protocol is transparent in describing our planned method for warfarin mapping and uses both prescription and test result data. We will also investigate gaps in prescribing to establish whether patients may have been in the hospital or having their OAC prescribed elsewhere; this is likely to be more common in this age group than others and has been noted as a limitation in other studies.^31^ A second limitation is that comorbidities may not always be recorded in the CPRD, particularly where they are diagnosed and treated in secondary care. However, as the comorbidities we have chosen are chronic and likely to have a significant impact on patients’ health, it is likely that they would be recorded accurately. Finally, as it is difficult to predict whether prescriptions for concomitant medicines are still continuing at any given time, we have decided to assume that if a prescription was issued in the 3 months prior to an OAC being started, the concomitant medicine is still continuing at that time. This is likely to be the case as most medications of interest are for chronic conditions. However, we acknowledge that it may overestimate exposure to these concomitant medications.

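### Objective 3 plans only crude comparisons of starters and untreated patients, which cannot by themselves show whether comorbidities influence prescribing; add an age- and sex-adjusted contrast or soften the wording

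*Protocol article*

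**What the plan says.** Under Statistical analysis, Objective 3 sets new OAC starters against patients not anticoagulated in the same period, for each of three periods. The planned output is:

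- For comorbidities and drugs: "The proportion of the cohort with each of the comorbidities and concomitant medications will be described".
- For the two risk scores, CHA2DS2-VASc and HAS-BLED: group means.
- For age, sex and lifestyle, percentages by category only.

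No stratification, standardisation or regression is stated for this objective.

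The purpose is stated elsewhere. Covariate classification says: "We want to investigate whether certain comorbidities influence the prescribing of OACs". The Discussion says: "This study will look at a number of different factors that may influence the prescribing of anticoagulants and how these have changed over time". The Introduction reports that the reasons physicians give for being "less likely to prescribe VKAs for a person with AF include advancing age, risk of falls, comorbidities and previous bleeding", so age is listed apart from the comorbidities.

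The other objectives that depend on age do handle it. For Objective 1, "Incidence will be stratified by age (75–84 and 85+) and sex". The Cox model of Objective 4 adjusts for age, together with covariates that Objective 3 identifies as important.

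The look-up date differs by group. Covariate classification collects "comorbidities accumulated up to the end of the time period for patients who do not receive an OAC or the OAC index date" for those who receive one.

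**The concern.** The aim under Covariate classification is explanatory: does having a comorbidity affect whether an OAC is started? The output under Objective 3 is descriptive. The two differ if the untreated group is older than the starters, which the reasons listed in the Introduction make plausible. Dementia, falls, fractures and renal impairment plausibly rise with age across the range from 75 upwards. Such a condition would then be commoner in untreated patients even if prescribers took no account of it, and a crude difference could not separate the condition from age.

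Sex matters mainly for one summary. Every patient is at least 75, so the age items of both scores are the same for all, but female sex adds a point to CHA2DS2-VASc. A difference in the share of women therefore moves the group means by that same difference (for example, 10 percentage points moves the mean by 0.10), whatever the comorbidities.

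At stake is the reading of the Objective 3 tables. A crude contrast might be reported as evidence that a condition deters prescribing when some or all of it reflects age.

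**Working it through.** The article states no sample size, age distribution by group or prevalence for Objective 3, so there is no figure to reproduce. What follows is an illustration, and every numerical input is an assumption.

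**Inputs**
- Age bands 75–84 and 85+, as used in Objective 1.
- s and u: assumed shares aged 85+ among starters and untreated patients.
- p0 and p1: assumed prevalence of a condition at 75–84 and at 85+, the same for starters and untreated patients inside each band. There is thus no association with prescribing once the band is fixed.

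**Formulas**
- Crude prevalence in starters: Ps = (1 − s)·p0 + s·p1.
- Crude prevalence in untreated patients: Pu = (1 − u)·p0 + u·p1.
- Crude odds ratio, untreated v starters: [Pu/(1 − Pu)] / [Ps/(1 − Ps)].

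**Worked example.** Take s = 25%, u = 50%, p0 = 8%, p1 = 20%.
- Ps = 0.75 × 0.08 + 0.25 × 0.20 = 11.0%.
- Pu = 0.50 × 0.08 + 0.50 × 0.20 = 14.0%.
- OR = (0.14/0.86) / (0.11/0.89) = 1.32.

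**Range**

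| Aged 85+, starters v untreated | Prevalence 75–84 / 85+ | Crude, starters v untreated | Crude OR | Age-stratified OR |
|---|---|---|---|---|
| 40% v 40% | 5% / 15% | 9.0% v 9.0% | 1.00 | 1.00 |
| 35% v 40% | 20% / 30% | 23.5% v 24.0% | 1.03 | 1.00 |
| 35% v 40% | 5% / 15% | 8.5% v 9.0% | 1.06 | 1.00 |
| 25% v 40% | 20% / 40% | 25.0% v 28.0% | 1.17 | 1.00 |
| 30% v 50% | 5% / 15% | 8.0% v 10.0% | 1.28 | 1.00 |
| 25% v 50% | 8% / 20% | 11.0% v 14.0% | 1.32 | 1.00 |
| 20% v 55% | 5% / 15% | 7.0% v 10.5% | 1.56 | 1.00 |

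The last column is 1.00 by construction. The crude OR is also 1.00 whenever prevalence does not rise with age, whatever the age gap.

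**Would the planned 95% intervals warn the reader?** Assume 5,000 patients per group.
- For 11.0% v 14.0%, the standard error of the difference is √[(0.11 × 0.89 + 0.14 × 0.86)/5,000] = 0.0066. The half-width is 1.3 points against a difference of 3.0 points, so the interval excludes zero.
- For 8.5% v 9.0%, the half-width is 1.1 points against a difference of 0.5, so the interval includes zero.

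Intervals describe sampling error only. They protect against a false reading when the age gap is small, not when it is large.

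**What age adjustment leaves in place.** Suppose prevalence is 20% in both groups at a common date, new diagnoses arise at rate r per year, and untreated patients are looked up L years later. Their prevalence becomes 1 − 0.80·exp(−rL).
- r = 0.01, L = 1: 20.8%, OR (untreated v starters) 1.05.
- r = 0.05, L = 4: 34.5%, OR (0.345/0.655)/(0.20/0.80) = 2.11.

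These rates and lags are also assumed. Stratifying by age or sex does not by itself remove this difference in look-up date.

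**The case against.** The strongest reply is that Objective 3 is descriptive. Its results are to be described and reported, and no odds ratio, test or model is planned. To show who was started and who was not, crude proportions are the right quantity. Age and sex appear by group and period with 95% confidence intervals, so an imbalance would be visible. The article is also a condensed account, and extra stratified tables are often left to an analysis plan. Stratifying rates in Objective 1 and adjusting a Cox model in Objective 4 serve other purposes, so nothing is contradicted.

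Most of this stands, and it limits the point. It does not dispose of the aim under Covariate classification, which asks about influence. A reader can see an age imbalance in the marginal percentages but cannot remove it from the comorbidity rows.

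A reader might infer more than the article supports:

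- *That the crude analysis is wrong, or is bound to mislead.* It is valid as description, and the age gap on which any distortion depends is not given.
- *That the identification of confounders promised in the Discussion is undermined.* That purpose concerns future comparisons between OACs, not starters against untreated patients, and a crude imbalance is an ordinary first look for candidate confounders.
- *That Objective 4 is damaged through its choice of covariates.* Its model already contains age, so a covariate carried forward only because it tracks age costs mainly some redundancy.
- *That a changing age gap will be misread as a change in prescribers' behaviour between periods.* This is possible, but nothing in the article shows that the gap changes.

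**Conclusion.** The point holds as a mismatch between a stated aim and the planned output. Objective 3 fixes crude proportions and mean scores. The protocol wants to learn whether comorbidities influence prescribing, and it names age as a separate reason for not prescribing. Crude figures alone cannot answer that question.

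The size is unknown. With no effect inside age bands, the assumed scenarios run from an odds ratio of 1.00 (matching age mixes), through 1.03 to 1.06 (35% v 40% aged 85+), to 1.56 (20% v 55%). The upper end needs both a wide age gap and a prevalence that rises steeply with age. The description itself is not invalid. This is an inexpensive improvement that would let the study come closer to its own question.

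**What to change.** In Objective 3, keep the crude proportions and add, for each period and each characteristic, an age- and sex-adjusted contrast of starters v no OAC. Either of these would do:

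- Report within the 75–84 / 85+ and sex strata already set for Objective 1.
- Standardise both groups to a common age–sex distribution, or fit a logistic regression of OAC start on the characteristic with sex and age at the covariate assessment date. Continuous age also deals with differences inside the two wide bands.

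Base any statement about influence on the adjusted contrast and word it as an association. State beside it that it does not remove the difference in look-up dates between the groups or confounding by other comorbidities.

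If the extra analysis is not wanted, soften the aim under Covariate classification so that it promises a description of differences only.

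The variables are already collected, and the cost is longer tables. Adjusted figures may also be given more explanatory weight than the design allows, which is why the accompanying caveat is needed.
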